## Abstract

**Background:**

Antenatal care is an important public health priority. Women from socially disadvantaged, and culturally and linguistically diverse groups often have difficulties with accessing antenatal care and report more negative experiences with care. Although group antenatal care has been shown in some settings to be effective for improving women’s experiences of care and for improving other maternal as well as newborn health outcomes, these outcomes have not been rigorously assessed in the UK. A pilot trial will be conducted to determine the feasibility of, and optimum methods for, testing the effectiveness of group antenatal care in an NHS setting serving populations with high levels of social deprivation and cultural, linguistic and ethnic diversity. Outcomes will inform the protocol for a future full trial.

**Methods:**

This protocol outlines an individual-level randomised controlled external pilot trial with integrated process and economic evaluations. The two trial arms will be group care and standard antenatal care. The trial will involve the recruitment of 72 pregnant women across three maternity services within one large NHS Acute Trust. Baseline, outcomes and economic data will be collected via questionnaires completed by the participants at three time points, with the final scheduled for 4 months postnatal. Routine maternity service data will also be collected for outcomes assessment and economic evaluation purposes. Stakeholder interviews will provide insights into the acceptability of research and intervention processes, including the use of interpreters to support women who do not speak English. Pre-agreed criteria have been selected to guide the decision about whether or not to progress to a full trial.

**Discussion:**

This pilot trial will determine if it is appropriate to proceed to a full trial of group antenatal care in this setting. If progression is supported, the pilot will provide authoritative high-quality evidence to inform the design and conduct of a trial in this important area that holds significant potential to influence maternity care, outcomes and experience.

**Trial registration:**

ISRCTN ISRCTN66925258. Registered 03 April 2017. Retrospectively registered.

**Electronic supplementary material:**

The online version of this article (10.1186/s40814-018-0361-x) contains supplementary material, which is available to authorized users.

## Background

Antenatal care is an important public health priority as it has the potential to impact positively on women’s health during pregnancy and upon the subsequent life course of women and their children. Women from socially disadvantaged and ethnic minority groups often have difficulties with accessing antenatal care [1] and report more negative experiences with care, despite having potentially complex social and medical needs [2]. Lack of engagement with antenatal care has been associated with adverse pregnancy outcomes including low birthweight, neonatal mortality and maternal mortality [3–5].

Group antenatal care combines conventional aspects of antenatal assessment with information sharing, including group discussion and learning, and the opportunity for social support for pregnant women. It is facilitated by health professionals (often midwives) for small groups of women with similar estimated due dates (and potentially their partners). To date, group-based models have been successfully implemented in a number of countries worldwide, including Australia [6], Sweden [7] and the USA [8]. Antenatal care configured in this way has been shown to increase women’s satisfaction with care and has improved health and safety outcomes such as pre-term birth and low birthweight [8–10].

Antenatal care for women in groups addresses multiple factors that have been found to be associated with women’s negative experiences of antenatal care [11–14]. As each appointment lasts for approximately 2 h (compared with approximately 15–20 min for a standard antenatal care appointment) and is facilitated by the same health professionals at each session, this model increases the amount of time that a pregnant woman spends with caregivers, e.g. midwives [6, 15], and enables continuity of carer [16]. It also provides for social support amongst group members, who, in our setting, may have become resident quite recently and/or may have migrated from abroad, where, for these and other reasons (e.g. financial constraints, limited English language ability), they may not have optimal existing support networks. Helping to address some of the main problems vulnerable and culturally and/or linguistically diverse women experience with standard, fragmented care, continuity of carer has been found to be beneficial, delivering enhanced communication and interpersonal rapport [17–19].

Furthermore, providing antenatal care within small groups promotes discussion and potentially, more effective learning for and amongst women, rather than solely relying on a health professional as the source of ‘expert advice’. It is also pertinent to note that many women living within the target areas do not currently have access to traditional antenatal education classes for various reasons. It is expected that this new approach will empower women, giving them more of ‘a voice’, enhancing informed decision making, and enabling them to tailor antenatal care more closely to their own needs. Significant benefits have been associated with such empowerment. If women feel that they have more autonomy and choice, this has been shown to increase their sense of control around birthing, and subsequently, this has the potential to increase their satisfaction with the birthing experience. Whether women experience birthing as a positive and affirming life event or as a traumatic, negative experience has the potential to affect their well-being and that of their children for the future life course [20–24]. The approach also encourages women to engage in more self-monitoring, with the aim of increasing knowledge and confidence; again, these factors have been shown to be significant in increasing the likelihood of a positive birth experience [25–28].

Although group antenatal care has been shown in other settings to be effective for improving women’s experiences of care and for improving other maternal as well as newborn health outcomes, these outcomes have not been formally assessed in the UK. A recent systematic review of group antenatal care concluded that more high-quality studies of its effectiveness are needed to establish whether positive findings are widely applicable [29]. These health improvements are in line with national and local aspirations for reducing inequalities and improving the health and well-being of women and children [23]. We are therefore proposing to evaluate robustly the effectiveness and cost-effectiveness of group-based antenatal care in enhancing women’s experience of antenatal care, increasing its relevance and value to women, and improving outcomes for mother and baby, particularly amongst women from ethnically, culturally and linguistically diverse and disadvantaged areas who are more likely to experience worse outcomes [30, 31]. This pilot trial is important to assess the best methods for conducting this proposed randomised controlled trial of this model of group antenatal care in the UK. Following best practice for pilot trials of complex interventions, pre-agreed progression criteria have been identified to inform the decision about whether to proceed, to proceed with amendments or not to proceed to a full trial (see Table 1) [32]. This paper relates to the pilot trial protocol version 2 (22.7.16) and adheres to the SPIRIT checklist reporting guidelines (Additional file 1).

**Table 1 Tab1:** Progression criteria to full trial

	Green light	Amber light	Red light
Recruitment—numbers of available women in each catchment	Within each catchment area, 60+ pregnant women with appropriate due dates	Within each catchment area, 40–59 pregnant women with appropriate due dates	Within the catchment area, less than 40 pregnant women with appropriate due dates
Recruitment—percentage who consent to randomisation	More than 40% who are eligible consent to randomisation	20–40% who are eligible consent to randomisation	Less than 20% who are eligible agree to randomisation
Uptake of group care model	8 or more of the 12 randomised take up the groups	6–7 of the 12 randomised take up the group	Fewer than 6 of the 12 randomised take up the group
Retention in groups*	5 remain in the group for 6+ sessions	4–5 remain in the group for 6+ sessions	Fewer than 4 women remain in the group for 6+ sessions
Follow-up response rate—self-complete outcomes questionnaire(s)	75% or greater response to follow-up	40–74% response to follow-up	Less than 40% response to follow-up

*Allowing for preterm births and moving out of the NHS Trust usual catchment area

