### Intervention

Following an extensive feasibility study, Pregnancy Circles are being implemented by a London NHS Trust as part of its service development. Initially, this was on a small-scale basis (four test groups in the feasibility work, followed by the three groups that form the focus of this pilot trial). Each Pregnancy Circle will consist of between 8 and 12 pregnant women who have estimated delivery dates within the same approximate 2- to 4-week period. The women who consent to participation in the study will be randomly assigned to one of two trial arms. One arm will receive standard antenatal care, whereas the other will receive all of their usual midwife-led antenatal care within a Pregnancy Circle. Any necessary appointments for consultant or specialist care will be carried out as per the usual care pathways outside of (and in addition to) the Circle.

Those women randomised to the group, antenatal care will start attending the ‘Pregnancy Circle’ for the first time at the routine midwife appointment (approximately 16 weeks of pregnancy) that follows their antenatal booking appointment (this usually takes place between 8 and 12 weeks of pregnancy). Subsequently, the women will continue to attend the Circle according to the normal antenatal care schedule. Any woman who chooses to discontinue her care in a group during pregnancy will transfer to the conventional care pathway. Any woman who does not attend the first Circle will be contacted by the facilitating midwives to ascertain the reasons for this. If non-attendance is due to pregnancy loss, they will be referred, by the facilitating midwives, to sources of ongoing support, such as their GP, as appropriate.

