### Sample size

The study will aim to recruit 24 participants from each of the three maternity units within the participating NHS Trust making a combined total of 72 women. Half of the recruited women in each area (up to 12 women) will be randomised to take part in the ‘Pregnancy Circles’ and half to receive standard antenatal care. This sample will not be powered to show differences between the trial arms on outcomes. Rather, the sample size has been determined to allow us to test the assumptions used in the sample size calculations for a full trial. This sample size will allow recruitment to take place in the three geographical areas in the NHS Trust where the Pregnancy Circles will take place, to allow us to test recruitment rates and to assess whether this differs by area. It will also allow us to explore uptake and retention rates to see whether our assumptions about the loss to follow-up are appropriate.

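### The retention row in Table 1 places exactly 5 retained women in both green and amber and gives no denominator, so it cannot show adherence among women randomised to a Circle

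*Protocol article*

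**What the plan says.** The progression criteria are in Table 1 of the protocol article (Background). For retention in groups the three cells read:

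- green: "5 remain in the group for 6+ sessions"
- amber: "4–5 remain in the group for 6+ sessions"
- red: "Fewer than 4 women remain in the group for 6+ sessions"

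A footnote to the row adds: "Allowing for preterm births and moving out of the NHS Trust usual catchment area". It does not say how the allowance is made.

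The uptake row just above does have a denominator; its green cell is "8 or more of the 12 randomised take up the groups". The Sample size section gives the same ceiling: "Half of the recruited women in each area (up to 12 women) will be randomised to take part". The Intervention section sets eight antenatal sessions and says that a woman who stops attending her Circle goes over to the conventional pathway.

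On the purpose of the pilot, the Sample size section says "the sample size has been determined to allow us to test the assumptions used in the sample size calculations for a full trial". It then links the study of uptake and retention to the assumptions about loss to follow-up. The section on pilot feasibility outcomes says that the observed rates will feed estimates for a full trial, and that progression is decided together with the Programme Steering Committee.

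**The concern.** Table 1 is the pre-agreed decision rule, so each result should fall in one cell and each cell should measure something the full trial depends on. The retention row fails on both counts. A result of exactly 5 has two classifications. A bare head-count also means different things in Circles of different size, and it is not expressed as a share of the women randomised, which is the population of an as-randomised comparison.

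This matters because leaving a Circle means receiving the comparator's care. Poor retention in the groups brings the arms closer together even if every woman returns her questionnaires. That is non-adherence, and it is distinct from loss to follow-up, the only full-trial assumption to which the Sample size section ties retention. No other row of Table 1 would reveal it: recruitment (two rows), uptake and questionnaire response could all be green while most women randomised to Circles attended fewer than 6 sessions.

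**Working it through.** **Inputs from the protocol article.** Women per area: 24, in three areas. Allocation: 1:1. Sessions: 8. Green uptake: 8 or more of 12. Retention cells: 5 (green), 4–5 (amber), fewer than 4 (red). The article gives no effect size, error rates, power or adherence assumption for the full trial.

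**The plan's own figure.** 3 × 24 = 72 women; 24/2 = 12 per Circle; 3 × 12 = 36 in the Circle arm. This reproduces.

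**Classifying each possible count, as printed.**

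- 0–3 retained: red only.
- 4 retained: amber only.
- 5 retained: amber and green.
- 6 or more retained: no cell literally covers it, because the green cell carries no comparator. The other four green cells do.

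If the missing comparator is at least 5, the overlap at 5 remains. If it is more than 5, the overlap disappears and the green minimum becomes 6.

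**What the count means as a proportion.** Attending 6 of 8 sessions is 75% of the programme.

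- 5 of 12 randomised = 41.7%, so 7 of 12 (58.3%) fall short.
- 6 of 12 randomised = 50%, if green means more than 5.
- 5 of 8 = 62.5%, if the denominator is the women who start at the green uptake minimum.

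The same count of 5 can thus stand for 42% or 62.5%, depending on a denominator that the row does not give.

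**Possible dilution in the full trial.** With s the share of the full effect that remains as randomised, the required sample size grows by about 1/s². The benefit models below are assumptions.

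1. *Only 6 or more sessions help.* s = 5/12 = 0.417; inflation 1/0.417² = (12/5)² = 5.76. At 6/12, s = 0.50 and inflation is 4.0.
2. *Benefit proportional to sessions; 8 start, 5 retained.* Low: the 5 attend 6 of 8 and the other 3 attend 1 of 8, so s = (5 × 0.75 + 3 × 0.125)/12 = 4.125/12 = 0.344. High: the 5 attend all 8 and the other 3 attend 5 of 8, so s = (5 × 1 + 3 × 0.625)/12 = 6.875/12 = 0.573. Inflation is about 8.5 and 3.0 respectively.
3. *Benefit proportional to sessions; all 12 start, 5 retained.* Low: (3.75 + 7 × 0.125)/12 = 0.385. High: (5 + 7 × 0.625)/12 = 0.781.
4. *Any attendance is enough; 8 start.* s = 8/12 = 0.667; inflation 2.25.

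**Illustration of power.** Assume a control rate of 50–60%, an undiluted effect of 8–12 percentage points and two-sided 5%. A trial sized for 80% power on the undiluted effect has about 21% power at s = 5/12. One sized for 90% has about 26–27%. None of these rates comes from the article.

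**The case against.** A reader might infer that Table 1 declares the full trial ready to proceed with an effect that is more than halved. The article does not support that reading, for these reasons:

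- Exactly 5 is also amber, and a comparator may simply have been lost from the green cell. If green means more than 5, the effect under the harshest model is halved, not more than halved.
- The denominator of 12 comes from the uptake row and the Sample size section, where it is a maximum. The footnote's allowance may raise the relevant share further.
- Retention is one of five criteria that inform a decision taken with the steering committee.
- Observed rates are already meant to feed full-trial estimates, so low adherence could be absorbed in the sample size. The full-trial calculation is not shown and may already allow for it.
- A loss of more than half follows from the all-or-nothing model. With benefit proportional to sessions, up to 78% of the effect could remain if all 12 start.

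All of this stands, and it limits what can be claimed about consequences. How lenient a green bound should be is also a design judgement.

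Two further inferences should be resisted. One is that 5 retained women contradicts the statement "Each Pregnancy Circle will consist of between 8 and 12 pregnant women". That describes membership, whereas the retention count is of women attending at least three quarters of the sessions, so the two do not conflict. The other is that midwife time rises to 240/5 = 48 minutes per woman per session. Women with fewer than 6 sessions still attend some, so 48 is an upper figure and not a typical one.

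The objection does not remove the overlap at 5, the absence of a denominator, or the fact that the stated use of retention is to check loss to follow-up and not adherence.

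**Conclusion.** The concern holds in a limited form. As printed, the row cannot classify a Circle with exactly 5 retained women, and it does not measure adherence among those randomised. The first point needs no assumption beyond the printed cells. Read against a full Circle of 12, green on both uptake and retention is compatible with 42% of randomised women attending 6 or more sessions, or with 50% if green means more than 5.

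The effect on a full trial is a possibility whose size depends on how benefit relates to attendance. At 8 starters and 5 retained, about 42% of the effect remains if only 6 or more sessions help, about 34–57% if benefit is proportional to sessions, and 67% if any attendance suffices. The article does not show that a full trial would be undersized. It leaves open how adherence will enter the full trial's sample size.

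**What to change.** In Table 1, rewrite the retention row so that:

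- the three cells are mutually exclusive and cover every possible result;
- retention is the proportion of all women randomised to Circles who attend 6 or more of the 8 sessions, pooled over the three Circles (up to 36 women) with each Circle also shown;
- the footnote says how preterm birth and moving away are handled, for example whether such women leave the denominator or have a reduced session target.

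In the Sample size section or the section on pilot feasibility outcomes, add that when the progression decision is made the full-trial size will be estimated with the observed adherence, and not only with the observed loss to follow-up.

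The cost is one table row, one footnote, one sentence and a line of arithmetic at the decision. No new data are needed, because attendance at each session is already recorded by the facilitating midwives. The downside is that green may become harder to reach.

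### Table 1's retention row puts exactly five retained women in both green and amber, and gives six or more no light if read literally

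*Protocol article*

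**What the plan says.** The Background section of the protocol article presents Table 1 as pre-agreed criteria that inform a three-way choice: proceed, proceed with amendments, or do not proceed. The section on pilot trial feasibility outcomes adds that a red result halts progression unless a suitable solution can be put in place, and that the Programme Steering Committee takes part in the decision.

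The retention row reads:
- green: "5 remain in the group for 6+ sessions"
- amber: "4–5 remain in the group for 6+ sessions"
- red: "Fewer than 4 women remain in the group for 6+ sessions"

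A footnote makes an allowance for preterm births and for women who leave the Trust's area.

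The uptake row gives green as "8 or more of the 12 randomised take up the groups" and amber as "6–7 of the 12 randomised take up the group"; red is anything below six. The Sample size section describes the number allocated to each Circle less rigidly: "Half of the recruited women in each area (up to 12 women) will be randomised" to the intervention.

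**The concern.** A traffic-light criterion agreed in advance is useful only if each possible result has one light. In the retention row the value five sits in two bands. If a Circle keeps five women, whoever reads the table can choose the light after seeing the result, and both choices agree with the text. The green cell also has no open upper end, so the better results, six and above, are not literally covered.

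The uptake row has one light for every count, but its cut-offs are tied to a denominator of 12 that the plan does not guarantee. If an area randomises fewer women to its Circle, the same counts stand for higher percentages, and good uptake can be graded down.

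**Working it through.** **The plan's own figures.** Three areas × 24 women = 72, and 24 ÷ 2 = 12 per Circle. Both reproduce, so the 12 in the uptake row is the planned number when recruitment is full.

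**Retention row.** Each count from 0 to 12 was tested against the three cells, under three readings of the green cell.

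| Women retained for 6+ sessions | Green = exactly 5 (as printed) | Green = 5 or more | Green = more than 5 |
|---|---|---|---|
| 0–3 | red | red | red |
| 4 | amber | amber | amber |
| 5 | green and amber | green and amber | amber |
| 6–12 | none | green | green |

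Reading green as five or more closes the gap at the top but leaves the overlap at five. Only the reading of more than five gives one light to every count, and the printed cell does not say that.

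**How often five could occur.** The article gives no expected retention, so this is an illustration only. Assume that women stay independently with probability p, that the three Circles are independent, and that each starts with n women. Then P(exactly 5) = C(n,5) p^5 (1−p)^(n−5), and P(at least one of three Circles at 5) = 1 − (1 − P)^3.

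| p | n = 8: P(5) | n = 8: any of three | n = 12: P(5) | n = 12: any of three |
|---|---|---|---|---|
| 0.5 | 0.219 | 52.3% | 0.193 | 47.5% |
| 0.6 | 0.279 | 62.5% | 0.101 | 27.3% |
| 0.7 | 0.254 | 58.5% | 0.029 | 8.5% |

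Five is a plausible result, especially in smaller Circles.

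**Uptake row.** At 12 randomised the cut-offs are 8/12 = 66.7% (green) and 6/12 = 50% (amber). The printed counts were compared with those same shares for Circles with 8 to 12 women randomised.

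| Randomised to the Circle | Counts where the printed light differs from the share-based light |
|---|---|
| 8 | 4 (50%) and 5 (62.5%): red, not amber; 6 (75%) and 7 (87.5%): amber, not green |
| 9 | 5 (55.6%): red, not amber; 6 (66.7%) and 7 (77.8%): amber, not green |
| 10 | 5 (50%): red, not amber; 7 (70%): amber, not green |
| 11 or 12 | none |

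Every difference is in the harsher direction. With 11 or 12 randomised, the counts and the shares agree.

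**The case against.** The strongest reply is that little depends on the overlap. Only red stops progression, the red retention cell is unambiguous, and the criteria inform a committee's judgement and do not replace it. That limits the consequence, and it is accepted. It does not remove the fault, because the committee still needs one light per result if the criteria are to count as agreed beforehand.

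A second reply is that nobody would leave six retained women ungraded when five is green. In practice that is probably so, and the missing light at six and above is a matter of literal reading. The overlap at five is not.

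A third is that a sign was lost when the table was read from PDF. A lost plus sign would mend the top end but not the overlap; a lost greater-than sign would mend both. Plus signs survive in the same row and elsewhere in the table, so this is unlikely, but a check against the typeset table would settle it.

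On uptake, the plan is for 12 per Circle. The Circle size of 8 to 12 in the Intervention section can be read as the number who attend, which fits green uptake out of 12. No section plans to randomise 8. What stands is that the words up to 12 allow fewer, and the row has not been written for that case.

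A reader might go further and infer that Table 1 as a whole fails to return an answer, because three catchments may differ and no rule combines three Circles. The text does not support that. The caseload row can naturally be scored one catchment at a time, and a condensed article may leave a combining rule to the full protocol.

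**Conclusion.** The retention row is wrong as printed: five retained women meets two lights, and this needs no assumption beyond the table's own words. The size is one cell boundary, green against amber. A reader might infer that the same data could be called go or no-go; they could not, since fewer than four is clearly red and neither disputed band touches it. Nor is a bare retention count a fault in itself, because a minimum number of women is a defensible standard for a group intervention.

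The uptake point is secondary and conditional. It applies only if 10 or fewer women are randomised to a Circle, within the range of 8 to 12 examined. In that case it can reach the red boundary: 5 of 8 (62.5%) would be red although it lies between the 50% and 66.7% cut-offs that apply at 12.

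The chances of landing on five rest on assumed retention of 50% to 70% and on independence. They show plausibility only.

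**What to change.** Before the results are seen, the sponsor and the Programme Steering Committee should record which retention bands were intended, and make them disjoint with an open top:
- green 5 or more, amber 4, red fewer than 4; or
- green 6 or more, amber 4–5, red fewer than 4.

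Keep the count per Circle. Table 1 gives no retention denominator, so turning the row into a percentage would bring in a cut-off that the sponsor did not set.

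For uptake, state each Circle's light as a share of the women randomised to it: green at least 8/12, amber at least 6/12 and below 8/12, red below 6/12. This leaves every light unchanged when 11 or 12 are randomised. Keep it per Circle, since pooling could hide a Circle that is red on its own.

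The cost is two edited rows and a dated committee minute. No new data or analysis is needed.
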